#### Secondary outcomes

In addition to the primary outcome, the study will analyze the effect of treatment on several secondary outcomes (see Table 1). Psychological well-being is measured with a six-item scale comprised of three, two-item subscales assessing emotional vitality (e.g., waking up fresh and rested, how much energy, and vitality the participant had), sense of positive well-being (e.g., how happy, satisfied, or pleased the participant has been in their personal life, whether daily life has been full of things that were interesting), and emotional self-control (e.g., whether the participant has been in firm control of their behavior, thoughts, emotions, or feelings, and whether the participant has been feeling emotionally stable and sure of themselves) [41]. Responses options are on a 6-point scale that ranges from (0) “not at all” to (5) “a lot or all of the time”, though the item assessing energy and vitality ranges from (0) “no energy at all, listless” to (10) “very energetic, dynamic”.

Work-related well-being is measured with three related constructs. Burnout is measured with two items that assess emotional exhaustion (e.g., “I feel burned out from my work.”) and depersonalization (e.g., “I have become more uncaring toward people since I took this job.”). These two items are taken from the Maslach Burnout Inventory [42] and have been validated as a measure of burnout [44]. Job satisfaction is a one item rating satisfaction with one’s job from 0 to 10. Engagement is measured on a Never-Always scale by focus on work (e.g., “At work, my mind is focused on my job.”),

Psychosocial work environment is assessed with 9 items from the Thriving from Work Questionnaire [45]. These items capture the perception of fair treatment, belonging, purpose, support, work-life balance, and fair pay. Voice environment was assessed with three items. Workers report on whether they know who to talk to when they have an issue at work, whether they can make suggestions without getting into trouble, and whether leadership takes their concerns seriously on a 6-point scale from (1) “never” to (5) “always or almost always” [46].

Other conditions of work are assessed with questions on job control and demands and safety climate. Job control and demands are measure with six items from the Job Content Questionnaire. Participants report on decision authority (2 items), skill discretion (2-items), and psychological job demands (2 items) on a 5-point scale from (1) “strongly disagree” to (5) “strongly agree” [47]. Safety climate (e.g., “I am provided with what I need to work safely,” and “Safety of workers is a big priority with supervisors and managers.”) is measured with 6-items assessed on a 5-point scale from (1) “strongly disagree” to (5) “strongly agree” [48–50]. As the study data collect spans the COVID-19 pandemic, a 5-item safety climate scale specific to COVID-19 is also included [51].

Self-reported health is measured with three separate items assessing different domains. General health is assessed using one item from the 36-item short form (SF-36) [52], which asks participants to rate their health from (1) “poor” to (5) “excellent”. Musculoskeletal pain is measured with a single item from the NordicQ [53]. Participants are asked whether they have experienced pain or aching (yes/no) in different body regions (e.g., back, shoulders/neck, hands/wrists/arms, and legs/knees/feet), and if yes, they are asked to rate the pain from (1) “mild” to (3) “severe”. One item from the Pittsburgh Sleep Quality Index [54] asks participants to report sleep duration in the last 30 days.

Injuries are assessed using both the questionnaire and administrative data. In the questionnaire, workers are asked whether they experienced an injury in the last 12 months, whether they reported the injury to management, and if it was not reported, the reason for not doing so. Administrative data captures the total injuries reported by the firm to the Occupational Safety and Health Administration (OSHA), as well as the Total Recordable Injury Rate (TRIR) by site. OSHA defines a recordable injury as any work-related fatality or injury that results in loss of consciousness, days away from work, restricted work, job transfer, or requires medical treatment beyond first aid [55].

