### Study design

The study is a two-arm cluster randomized-controlled trial. The units of analysis are individuals within the cluster of fulfillment centers. There are three measurement time points: baseline measured prior to randomization (T1), 6 months after baseline (T2), and 12 months after baseline (T3). Process evaluation data will be collected for approximately 30 months, from baseline through 18 months after the T3 survey. The study has been registered with the ClinicalTrials.gov registry (NCT05199415) and approved by the Institutional Review Board (IRB) at the Massachusetts Institute of Technology (Protocol: 200800024). Any changes to the protocol will be approved by the IRB.

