### Randomization

Following baseline survey administration, fulfillment centers are matched based on the main picking technology (conveyors, carts, or robotics) and size (small, medium, large, or very large) based on the number of workers within the fulfillment center. Within each technology and size group, each fulfillment center is randomized to either receive the intervention or to maintain operations as usual. Randomization occurred by randomly assigning numbers to be intervention or control and then randomly assigning them to study buildings. Site managers are then notified of their fulfillment center’s treatment assignment. Given the geographic distance between fulfillment centers, the likelihood of contamination between sites was considered minimal.

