**Fig 2 pone.0305334.g002:**
[figure not shown]
Health and Well-Being Committee participatory intervention model.

HaWCs will be composed of 10–14 frontline workers and supervisors and led by a “co-lead” pair, comprised of one frontline worker and one supervisor. The dual management-worker leadership structure is designed to facilitate a joint problem-solving orientation with a focus on multiple stakeholder interests and mutual gain. Members of the HaWC are expected to be volunteers and to represent different departments, tenure, and social identities (e.g., gender and race). HaWC meetings will occur when associates and supervisors are “on the clock” and compensated for their time. HaWCs are designed to be a new formal voice channel where workers can submit concerns about the workplace environment pertaining to safety (e.g., physical hazards), the psychosocial environment (e.g., how workers feel about their treatment at work), and work organization (e.g., workflow, training opportunities, scheduling). HaWCs then will be charged with prioritizing concerns, designing, coordinating, and implementing solutions, and tracking outcomes.

Following randomization, managers in intervention sites will meet with the research team to plan the intervention launch, identify possible co-leads, and plan recruitment of HaWC members. Co-leads will then participate in a multi-session training delivered by the research team where they will be trained in the continuous improvement strategies and facilitation skills.

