### Outcome measures

Table 2 presents a description of the outcomes measured in the study. All outcomes are measured at each of the three timepoints in both treatment and control sites.

**Table 2 pone.0305334.t002:** Overview of outcome measures.

Outcome	Source	Description

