**Secondary**		
Psychological well-being	Questionnaire	Six items assessing emotional vitality, sense of positive well-being, and emotional self-control in the last month [41].
Work-related well-being	Questionnaire	Burnout: Two-item Maslach burnout scale [42]. Job satisfaction: One item rating satisfaction with the job from 0–10. Engagement: Two items assessing whether a worker’s mind is focused on their job and whether their job is boring.
Psychosocial work environment	Questionnaire	Nine items from the Thriving from Work Questionnaire that assess perceptions of fair treatment, respect, belonging, purpose, support, work-life balance, fair pay, and job security.
Voice environment	Questionnaire	Worker voice: Three items reporting on whether workers know who to talk to when they have an issue at work, whether they can make suggestions without getting into trouble, and whether leadership takes their concerns seriously.
Conditions of work	Questionnaire	Job demands and control: Six items on decision authority, skill discretion, and psychological job demands. Safety climate: Six item safety climate scale and additional safety climate items specific to the COVID-19 pandemic.
Self-reported health	Questionnaire	General Health: A single general item from SF-36. Musculoskeletal pain: A single modified item from the NordicQ. Sleep: A single item assessing sleep duration in the last 30 days from the Pittsburgh Sleep Quality Index.
Injuries	Questionnaire Administrative Data	Questionnaire: Three items asking whether an injury was experienced, whether it was reported, and the reason for not reporting. Administrative data: Captures total injuries reported to Occupational Safety and Health Administration and number of recordable injuries per 100 workers, by site.

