### Data analysis

Preliminary data analyses will include descriptive statistics by study arm (intervention or control) to summarize characteristics of workers and fulfillment centers. In the primary analysis, the effect of the intervention on the primary and secondary outcomes will be investigated using intention-to-treat (ITT) analyses with multilevel linear mixed models for continuous outcomes and generalized mixed effect models for binary outcomes. Models will include random intercepts for clusters and workers within each site, a fixed effect for each stratum, a fixed effect for each follow-up time point (T1 and T2), and an interaction effect between intervention status and follow-up time. The interaction between intervention status and follow-up time will explicitly test for intervention effects. All models will be adjusted for covariates, such as age, race, gender, calendar time, and site level policy changes, as appropriate. While the primary analysis will be ITT, exploratory analysis will consider whether number of HaWC action projects and a coded typology of projects (e.g., safety focused vs. operational vs. focused on the broader psychosocial environment) affects the impact of the intervention.

As a secondary analysis, another model will be fit among workers who have participated in baseline and at least one follow-up survey to directly control for baseline values of outcomes of interest. Both the primary and secondary analysis will include calendar time to account for changes in the larger environment, such as seasonal fluctuations in demand, seasonal changes in distress, and pandemic variations in COVID-19 death rates. Sensitivity analysis will include an assumption of non-ignorable missingness based on an imputation approach developed specifically for longitudinal data [56]. Estimates from mixed-model regressions will be considered valid when missingness across assessment time-points is missing at random (MAR), assessed using logistic regressions for response bias [57, 58].

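### The survey injury item looks back 12 months but is analysed 6 months after baseline, so the T2 injury effect is attenuated by about half on the relative scale

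*Protocol article*

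**What the plan says.** All references are to the Methods of the protocol article.

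- **Recall period.** Under Secondary outcomes, "workers are asked whether they experienced an injury in the last 12 months". No other recall period is given for any wave.
- **Status.** Table 2 lists questionnaire injuries as a secondary outcome: "Three items asking whether an injury was experienced, whether it was reported, and the reason for not reporting".
- **Waves.** Study design sets the measurements as "baseline measured prior to randomization (T1), 6 months after baseline (T2), and 12 months after baseline (T3"). Outcome measures adds: "All outcomes are measured at each of the three timepoints in both treatment and control sites".
- **Order of events.** Under Randomization, "Following baseline survey administration, fulfillment centers are matched", and sites are then allocated. The Intervention section continues: "Following randomization, managers in intervention sites will meet with the research team to plan the intervention launch".
- **Model.** Data analysis applies the same approach to primary and secondary outcomes, with "generalized mixed effect models for binary outcomes" and random intercepts for sites and workers. It states: "The interaction between intervention status and follow-up time will explicitly test for intervention effects". That section labels the follow-up time points T1 and T2. Whether T2 and T3 was meant or not, T2 is among the times tested.

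**The concern.** The recall window is twice as long as the interval between waves. A yes at T2 may refer to an injury from before the sites were randomized, which the intervention could not have prevented. The interaction at T2 is nevertheless read as an intervention effect on injuries.

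This mismatch is specific to the injury item. The K6 and the well-being scale refer to the last month and the sleep item to the last 30 days, so those windows fit well inside a 6-month interval.

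At stake is how the 6-month survey-injury result is read. It is pulled toward no effect by construction. If T3 then shows a larger effect, part of the apparent growth between T2 and T3 comes from the question and not from the intervention.

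**Working it through.** The article states no injury rate, effect or power, so there is no figure of the plan to reproduce.

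**1. Windows, in months from baseline, with a 12-month recall**

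| Wave | Window | Before baseline |
|---|---|---|
| T1 | -12 to 0 | 12 of 12 |
| T2 | -6 to +6 | 6 of 12 (50%) |
| T3 | 0 to +12 | 0 of 12 |

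T1 and T2 share 6 months, T2 and T3 share 6 months, and T1 and T3 share none. Randomization comes after the baseline survey, so for a worker employed throughout, 50% is a minimum.

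**2. Attenuation of the rate ratio.** Assume a constant injury rate and a rate ratio RR that applies from baseline. With s = 6/12 of the window after baseline, the apparent ratio is (1 - s) + s x RR:

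- RR 0.80: 0.5 + 0.5 x 0.80 = 0.90
- RR 0.70: 0.5 + 0.5 x 0.70 = 0.85
- RR 0.50: 0.5 + 0.5 x 0.50 = 0.75

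**3. The same for a yes/no answer.** Let p0 be the control 12-month risk and L = -ln(1 - p0). The treated risk at T2 is 1 - exp(-L x [(1 - s) + s x RR]). With p0 = 10%, L = 0.1054. For RR = 0.80 the treated risk is 1 - exp(-0.1054 x 0.90) = 9.05%, a risk ratio of 0.905. For RR = 0.70 it is 8.57%, a risk ratio of 0.857.

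A 6-month recall at T2 would lie wholly after baseline. Over assumed values of p0 (5%, 10%, 20%) and RR (0.5, 0.7, 0.8), the 12-month recall keeps 0.42 to 0.50 of the log odds ratio that the 6-month recall would show, and 0.39 to 0.47 of the log risk ratio. On the absolute scale it keeps 0.89 to 0.97 of the risk difference. There the main cost is noise from injuries before baseline.

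**4. Turnover.** Power calculations gives 28% turnover per 6 months, and all current workers are invited at each wave. Suppose the item counts only injuries in this job, and 28% of T2 respondents are new hires with on average 3 months in post (an assumption). The share of recalled time before baseline is then 0.72 x 6 / (0.72 x 12 + 0.28 x 3) = 4.32 / 9.48 = 46%. A steady-state tenure distribution with the same turnover gives 42%. Both remain close to half.

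**5. Power.** Using the ranges of step 3, suppose a 6-month recall would give 80% power at T2. Ignoring clustering, a 12-month recall gives:

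- 43% to 48% for a comparison of arms at T2 alone, on the odds or the risk-difference scale;
- 75% to 79% for the T2-minus-T1 change in risk when every worker answers both waves, because the shared 6 months largely cancel.

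The planned model lies between these cases, depending on how many workers are seen twice. The article does not fix that proportion for this item.

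**The case against.** The strongest case on the other side is one of scope. This is one item within one of several secondary outcomes, at the intermediate wave of a 12-month intervention. The T3 window lies after baseline, the model already estimates a T3 effect, and injuries are also taken from company records. All of that stands, and it limits the weight of the point. The records do not replace the item, though. They are described as injuries reported by the firm and as site rates, while the survey also asks about injuries that were not reported to management.

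Several stronger readings are tempting, and the document does not support them.

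- *Power at T2 falls from 80% to 29%.* A reader might halve the effect and keep the standard error: Phi(2.802/2 - 1.96) = 0.29. That takes as benchmark a 12-month window wholly after baseline, which cannot exist 6 months after baseline.
- *Start-up of the committees makes the dilution worse.* A slow start would weaken any T2 outcome under any recall window. It is not a consequence of the 12-month question.
- *One injury is counted as two independent outcomes.* The item records whether an injury occurred, not how many, and the model has a random intercept for each worker. The same injury can produce a yes at two waves, and the intercept does not reproduce the overlap exactly, but the answers are not treated as independent.
- *The report will show no effect at 6 months and an effect at 12.* Attenuation is not absence of effect, so this is only a possible misreading.

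The questionnaire is not shown, so wording that differs by wave cannot be ruled out. The article, however, states 12 months without qualification.

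**Conclusion.** The mismatch is real and follows from the stated recall period, wave timing and model. At T2, at least half of the window precedes randomization for a worker employed throughout, and the intervention effect is attenuated by about half on the relative scale (0.80 appears as about 0.90). The baseline measurement and the worker intercept do not take the earlier injuries out of the T2 answer.

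The size rests on a constant injury rate, an effect that starts at baseline, and the assumed risks and rate ratios above. It applies to odds or risk ratios, the natural scale for the planned binary model. The risk difference itself is nearly unchanged from what a 6-month recall would give. The loss of power at T2 cannot be given as one number. The finding does not extend to the T3 contrast, the administrative injuries or the primary outcome. It is worth correcting because the analysis remedy is nearly free.

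**What to change.** **Analysis.** State that for the survey injury item the intervention contrast is T3 (window after baseline) against T1 (window before baseline). These two windows do not overlap. Do not test or interpret the T2 interaction for this item as a 6-month effect. T2 answers may be described by arm, with a note on the window. The cost is a sentence in the analysis section and the loss of the T2 survey-injury estimate.

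**Questionnaire, only if it can still be changed.** Ask at both follow-up waves about injuries since the previous survey (6 months). Changing T2 alone would leave T2 and T3 with different windows in one repeated-measures model. T1 would still refer to 12 months, so a within-arm change from baseline could not be read as a change in injury rate. Roll-out ran from July 2021 to July 2022, so this option may no longer be open.

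**Administrative data.** Use company injury records for a 6-month effect only if they are available by period. The article mentions totals and site rates, and no injury dates.

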### Covariates

Worker characteristics, including age, gender, race and Hispanicity are captured with administrative data and linked to the survey data. Additional personal characteristics (marital status, children at home) are self-reported in the questionnaire. Tenure with the firm, department, hourly wage, part-time vs full-time job, and shift are included through administrative data.

### Data management and sharing

All survey data will be collected using the Qualtrics platform. Data will be downloaded from Qualtrics frequently during the survey period and kept on a secure server only accessible to the data team. Though the survey will collect identifiable information for the purposes of incentive distribution, participants’ data will deidentified immediately after their incentive is sent. Given the low-risk nature of this study, a data monitoring committee is not needed. Survey data will be available through a restricted access process after the acceptance for publication of the main findings. Those who wish to use the data will need to complete an application with their affiliate institution’s IRB and provide a brief description of their project. The data sharing agreement will state that a) the data access will last for one year, with the opportunity to extend on a case-by-case basis, b) those who use the data will do so only for research or statistical purposes and not for investigation of the research subjects, c) published paper will include the appropriate acknowledgement as stated in the data documentation, and d) the data will not be distributed to anyone other than the approved researcher.

### Data analysis

Preliminary data analyses will include descriptive statistics by study arm (intervention or control) to summarize characteristics of workers and fulfillment centers. In the primary analysis, the effect of the intervention on the primary and secondary outcomes will be investigated using intention-to-treat (ITT) analyses with multilevel linear mixed models for continuous outcomes and generalized mixed effect models for binary outcomes. Models will include random intercepts for clusters and workers within each site, a fixed effect for each stratum, a fixed effect for each follow-up time point (T1 and T2), and an interaction effect between intervention status and follow-up time. The interaction between intervention status and follow-up time will explicitly test for intervention effects. All models will be adjusted for covariates, such as age, race, gender, calendar time, and site level policy changes, as appropriate. While the primary analysis will be ITT, exploratory analysis will consider whether number of HaWC action projects and a coded typology of projects (e.g., safety focused vs. operational vs. focused on the broader psychosocial environment) affects the impact of the intervention.

As a secondary analysis, another model will be fit among workers who have participated in baseline and at least one follow-up survey to directly control for baseline values of outcomes of interest. Both the primary and secondary analysis will include calendar time to account for changes in the larger environment, such as seasonal fluctuations in demand, seasonal changes in distress, and pandemic variations in COVID-19 death rates. Sensitivity analysis will include an assumption of non-ignorable missingness based on an imputation approach developed specifically for longitudinal data [56]. Estimates from mixed-model regressions will be considered valid when missingness across assessment time-points is missing at random (MAR), assessed using logistic regressions for response bias [57, 58].

Beyond the primary and secondary analysis, intervention effects will be measured with voice environment as a primary mediator. Both the difference and product method will be used in mediation analysis; the latter can incorporate possible mediator-intervention interaction. The results of these models will be used to obtain indirect effects of the intervention on outcomes of interest. Process data will also be used to measure intervention effects that reflect differential intervention implementation.

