### Blinding

Participants undergoing baseline measurement are unaware of arm allocation as randomization occurs after baseline. Due to the nature of the intervention, it will not be possible to blind participants throughout the data collection process. However, all recruitment materials will describe the study goals quite broadly *(e*.*g*., “The purpose of the study is to understand what it’s like to work at a fulfillment center in general and to understand how changes in the workplace affect your experience working at [Sigma]”) and will not mention the intervention. Additionally, those conducting final data analyses will be blinded to group allocation.

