### Data collection and measures

Table 1 provides an overview of data collection activities, aligned with overall study objectives.

**Table 1 pone.0305334.t001:** Overview of study objectives and supporting research methods.

Study Objective	Supporting Research Method
Evaluate the efficacy of the HaWC intervention and its effect on health outcomes and changes in the conditions of work	Self-reported surveys from workers in HaWC and control sites (T1, T2, T3)
	Administrative data collection for all sites, including turnover rates, other changes in workplace policies or practices
Conduct a process evaluation of key contextual factors that support effective and integrated intervention implementation and sustained engagement	Tracking meetings and projects in HaWC sites (detailed tracking through T3, summaries after)
	Co-lead interviews in HaWC sites (every 6 months)
	Manager interviews in HaWC and control sites (T2, T3)
	Focus Groups in HaWC sites (T3)

Survey measurement occurs at three time points: baseline (T1), 6 months (T2), and 12 months (T3). At each time point, all workers currently working in the fulfillment center are presented with an individualized invitation letter to complete a web-based survey via Qualtrics. Participants can access the questionnaire using a cell phone, research-team provided tablets, or desktop computers at the worksite. All participants will provide informed consent prior to participation. All participants are given the opportunity to participate in the survey while on-the-clock, but also have the option to participate outside of work. To promote participation, all individuals who complete the questionnaire are given a small incentive at each wave. Those who complete the questionnaire are also eligible to receive site-level raffles. In addition to the self-reported questionnaires, administrative data on worker characteristics and injuries and fulfillment centers-level characteristics are collected from Sigma databases.

Given the low-risk nature of the study, adverse events are unexpected. However, to ensure safety of study participants, the research team will proactively ask building managers whether concerns have arisen about the study. Should any concerns arise, participants will be able to contact the IRB and Human Resources department at Sigma.

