### Process evaluation

In addition to the cluster randomized trial, the study will involve a process evaluation to examine intervention fidelity and investigate the dynamic of organizational change. Robust process analysis is particularly important for participatory interventions such as the HaWC program because the targeted changes will vary across sites. Specifically, the process evaluation aims to answer the following research questions: (1) What organizational and contextual factors (e.g., institutionalized power differentials, social identities, and group processes) shape the scope and type of action plans that HaWCs prioritize and adopt? (2) What barriers or challenges do participants face in implementing the intervention and what supports the effective resolution of those difficulties? (3) What factors facilitate sustained engagement once the research team is less involved, i.e., during the maintenance phase of the intervention? To answer these questions, data will be collected at regular intervals from various sources in the intervention sites, including HaWC members (focus groups), HaWC co-leads (repeated interviews), and fulfillment center managers (repeated interviews) (Fig 3). Additionally, the research team will take detailed field notes while observing the HaWC meetings and following interviews. Interview topics include experiences with HaWC processes, HaWC adaptations, barriers to implementation, and any site-specific context that may influence the intervention. Managers at control sites are interviewed at 6, 12 and 30 months (in parallel with manager interviews in treatment sites) to assess any changes in fulfillment center technologies, policies, and practices.

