### Strengths

The research team expects the strong causal design, multi-method data, and participatory intervention to provide critical information on the feasibility and efficacy of Health and Well-Being Committees in the important context of fulfillment centers. Studying frontline workers in the warehousing and storage industry is valuable not only because this is a rapidly growing yet understudied sector, but also because research on interventions to improve well-being in low-wage workers in general, is extremely limited. ^24^

Another innovation is the combination of a mental health primary outcome (psychological distress) with analysis of potential impact on positive psychological well-being (emotional vitality). With a strong causal design that utilizes a randomized field trial, the project will provide an evidence base for evaluating the efficacy of a participatory intervention not only to reduce psychological distress, but also to promote well-being, and to improve work conditions among fulfillment center workers. Additionally, the use of a randomized cluster trial provides the opportunity to isolate the intervention from other changes in Sigma’s work environment, including COVID-19 related confounders, and organizational policy changes that may occur. A pre- and post-test study would not be sufficient to tease out these confounders, but the trial allows the team to isolate the treatment’s impact.

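### All models, including the primary ITT model, may adjust for post-randomization site policy changes with no limit to changes independent of arm, so the covariate may be partly a mediator

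*Protocol article*

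**What the plan says.** The Data analysis section describes the primary analysis as intention-to-treat, using mixed models, and names the term that carries the result: "The interaction between intervention status and follow-up time will explicitly test for intervention effects". It then gives one covariate rule for every model: "All models will be adjusted for covariates, such as age, race, gender, calendar time, and site level policy changes, as appropriate". The Covariates section neither lists nor defines policy changes.

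The Blinding section fixes the timing: "Participants undergoing baseline measurement are unaware of arm allocation as randomization occurs after baseline". Anything recorded during follow-up is therefore post-randomization. Table 1 lists one record of such changes: "Administrative data collection for all sites, including turnover rates, other changes in workplace policies or practices". The Process evaluation section adds manager interviews, in control sites at 6, 12 and 30 months and in parallel in treatment sites, which ask about changes in technology, policy and practice.

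The Intervention section says what the committees are for: "HaWCs then will be charged with prioritizing concerns, designing, coordinating, and implementing solutions, and tracking outcomes". One of their three domains is "work organization (e.g., workflow, training opportunities, scheduling". The Process evaluation section adds that "the targeted changes will vary across sites", so the intended changes are site-level.

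The Strengths section argues that "a randomized cluster trial provides the opportunity to isolate the intervention from other changes" in the firm's work environment, and counts organizational policy changes among those other changes.

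**The concern.** An ITT analysis estimates the total effect of assigning a site to a committee, by whatever route that effect arises. If a committee obtains a new scheduling or training practice and this is recorded as a site policy change, that change lies on the path from assignment to distress. Conditioning on it removes that path from the estimate. What remains is an effect not passing through policy, usually smaller than the total. Where unmeasured site factors drive both policy changes and distress, conditioning on a consequence of arm can also introduce bias whose direction cannot be predicted.

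Two further consequences follow. With few sites, a covariate that tracks arm is collinear with it and can widen the standard error. The planned mediation analysis through voice environment includes the difference method, which compares the intervention coefficient with and without the mediator. If another possible mediator is already in every model, that comparison does not start from the total effect.

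**Working it through.** **1. Is the covariate post-randomization?** Randomization follows the baseline survey. The administrative record in Table 1 has no stated cut-off, and the manager interviews begin at 6 months. The Data analysis section does not say which source feeds the covariate, so the link to these records is an inference. No other source is described, and no date limit is given.

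**2. Can arm affect it?** The committees' domains (safety, psychosocial environment, work organization) overlap with what a site would record as a policy or practice change. The Limitations section says that building managers act with considerable autonomy, so a manager's own decision may also respond to a committee.

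**3. What does adjustment do?** Write the total effect as T = D + I, where I passes through recorded policy changes and D does not. A model with the policy variable coded as time-varying estimates D. With mediated share s = I/T, the coefficient is (1 − s)T. If the variable enters as a time-constant site main effect, it is nearly orthogonal to the within-site arm-by-time contrast and removes little. The article does not say which coding is meant.

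**4. Illustration of size.** The documents give no mediated share, so s is assumed. The starting point is the Power calculations section: 0.13 SD, 0.56 K6 points and 90% power at 66% response. No alpha is stated there; two-sided 0.05 is assumed, with the standard error unchanged.

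- 90% power implies effect/SE = 1.960 + 1.282 = 3.242.
- Power with share s = Φ((1 − s) × 3.242 − 1.960).

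| s | Effect left (SD) | K6 points left | Power |
|---|---|---|---|
| 0 | 0.13 | 0.56 | 90% |
| 25% | 0.0975 | 0.42 | Φ(0.47) = 68% |
| 50% | 0.065 | 0.28 | Φ(−0.34) = 37% |
| 75% | 0.0325 | 0.14 | Φ(−1.15) = 12.5% |

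**5. Simulation check.** This used 21 sites (10 and 11, as in the power section), least squares on site means, and 4,000 runs per scenario. It assumed a site-mean residual SD of 0.04 and a policy score with SD 0.5 within arm, one unit higher in the intervention arm.

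- Without the covariate, the arm coefficient recovered 0.13 SD at every s.
- With it, the coefficient was 0.098, 0.066 and 0.033 SD at s = 25%, 50% and 75%.
- With s = 0 (the score tracks arm but does not affect the outcome), the mean stayed at 0.13 SD, but the SD of the estimate rose from 0.018 to 0.026.
- With a score unaffected by arm but prognostic (assumed coefficient 0.065 per unit), both models gave 0.13 SD, and adjustment lowered the SD of the estimate from 0.023 to 0.018.

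This is a simplification: the planned model is longitudinal, with baseline data and random intercepts. It shows the direction of the effect for a covariate that moves with arm, not its size in this trial.

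**The case against.** The strongest reply is that the article already separates committee output from background change. Table 1 tracks committee meetings and projects as process data, apart from the administrative record of other changes. Immediately after the covariate sentence, the Data analysis section assigns the number and type of committee projects to exploratory analysis and contrasts this with the ITT primary analysis. The Strengths section speaks of outside changes in the firm. Read together, these suggest that the covariate means changes not produced by the committees. The list is also open-ended and qualified, and exact definitions may sit in an analysis plan that is not shown.

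Much of this stands. A reader might infer that part of the effect will certainly be adjusted away; the documents do not support that, because the loss is zero if only arm-independent changes are coded and small if the coding is time-constant. A reader might also take the Strengths statement to contradict the adjustment. It does not: randomization removes the need to adjust for unbiasedness, but adjusting for outside changes can still gain precision, as the last simulation scenario shows.

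What does not stand is that the wording is already safe. The separation in Table 1 is not carried into the model statement. The qualifier gives no rule for deciding what belongs in the primary model. Labelling a change as outside the committee also does not make it independent of arm when the site manager may be responding to the committee. Firm-wide changes that reach both arms together are largely absorbed by calendar time, already in the model, so what is left for this covariate is mainly site-specific variation, the part a committee could influence.

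**Conclusion.** The point holds as a risk created by the wording. The text permits the primary model to condition on a site-level variable recorded after randomization that the intervention is designed to influence. To the extent that recorded changes result from assignment, and are coded as varying over time, the intervention-by-time coefficient is not the total ITT effect and would usually lie closer to zero.

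The documents do not allow the loss to be sized. No figure in the table above, including the 37%, should be read as the trial's expected power: each rests on an assumed share, an assumed alpha and an unchanged standard error. The protocol's named primary mediator is voice environment, not policy, so nothing in it indicates how large the policy share might be. This should be fixed because it bears on what the primary coefficient means, but it does not show that the estimate will be biased.

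**What to change.** Remove site-level policy changes from the primary and secondary ITT models. Keep stratum, covariates fixed before randomization, and calendar time. Use recorded policy changes in the mediation or process analyses, or in a labelled sensitivity analysis.

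If the team wants to keep the covariate in the ITT models, define it in advance as changes dated before randomization or imposed firm-wide regardless of arm, and state its source and coding. Sorting site-level changes into outside and committee-driven after the fact would be a matter of judgment.

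The cost is a wording change and no new data. If outside changes are strongly prognostic, dropping them loses some precision; the restricted definition keeps whatever part of that precision comes from changes meeting it.
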